### Development of the Intervention

The intervention consists of a Web-based ulcer record to facilitate asynchronous communication between primary and specialist health care and includes a database and an application to communicate images and text between participants. The Web-based ulcer record (Dansk Telemedicin AS) has been adapted to Norwegian legislation and is described in a previous publication [24]. We carried out a preliminary project in spring 2011 to develop and adjust the telemedicine tools to patients with diabetes-related foot ulcers receiving care in the community. In a pilot project between autumn 2011 and spring 2012, the data collection forms and telemedicine tools were tested on five patients. A standard procedure protocol was developed in brochure form to ensure that photographic documentation of ulcers was taken at optimal resolution, with adequate lighting and good contrast, from specified angles. The brochure also included instructions for use of the Web-based ulcer record, the integrated infrastructure, and legal and data security aspects.

### Telemedicine Intervention

Patients in the intervention group receive telemedicine follow-up care in the community. The key ingredient in the intervention is the close integration between health care levels. The intervention is facilitated by the use of an interactive wound platform consisting of a Web-based ulcer record combined with a mobile phone, enabling counseling and communication between nurses in the community and specialist health care. Foot ulcer data including images are sent by mobile phone to the Web-based ulcer record for asynchronous consultation with specialist health care. Images are recorded throughout the trial, stored in the Web-based ulcer record, and transferred encrypted to a server. General practitioners in the intervention group can get access to the Web-based ulcer platform if required (Figure 2).

The nurses are trained to use the Web-based ulcer record and mobile phone using written information. Individual teaching and training of the nursing staff in primary care is offered at the specialist clinic or in primary care to secure equivalent and competent handling of patients. The diabetes specialist nurse and/or podiatrist in the multidisciplinary project team provide the latter. The written information also includes a section defining the delegation of responsibility at each level of health care providers with respect to the treatment of diabetic ulcers. Follow-up procedures are set up for each participant. The nurses review the images at the Web-based ulcer record and discuss them with the specialists if there is any uncertainty. Nurses in the specialist health care communicate with community care nurses at least once a week. In addition, nurses in specialist health care can check and contact community nurses on an ongoing basis. Discussions are mainly about wound care but could also include earlier referral if required. The home care nurse or general practice nurse will initiate contact with specialist health care regardless of prior agreements if the ulcers do not improve or get worse.

We have not made important changes to the intervention or control arm during the trial. Functionality has been evaluated every year and minor adjustments have been performed; however, this has not involved system failures/downtimes, etc. We have used the same photo documentation (smartphone/camera) throughout the project.

**Figure 2 figure2:**
[figure not shown]
Diagram illustrating the general use of the telemedicine tool.

### Control Group

The control group receives standard hospital outpatient consultations with health care professionals at the endocrinology unit of Stavanger University Hospital. The medical treatment given to the control and intervention group is based on the same procedures. Foot ulcer data including images are recorded throughout the trial but only at the outpatient clinic. Like in the intervention group, the data are stored in the Web-based ulcer record and transferred in encrypted form to the same server.

### Evaluation Measures

The trial includes self-reported questionnaire data and information collected from the electronic patient journal and the clinical diabetes system at the outpatient clinic. The quantitative measures in our trial are described in detail below.

#### Primary Outcome Measure

The primary outcome is healing time measured from the time the person presents the ulcer at the clinical site (included in the trial) until the foot ulcer is healed.

#### Secondary Outcome Measures

Time to amputation (foot, below, through, or above the knee) and death during the patient follow-up period as well as self-reported questionnaire data will be used as secondary outcome measures in this trial. This questionnaire package will include standardized instruments measuring patient-reported outcomes as problem areas in diabetes, quality of life, symptoms of anxiety and depression, and satisfaction with treatment (see Table 1 for details).

**Table 1 table1:** Summary of measures.

Outcome		Data collection instrument	Time points^a^
**Primary outcome**			
	Healing time	Time to healing. Data from electronic medical journals at the clinical sites.	t2

**Other measures**			
	Demographic characteristics (age, sex, ethnicity, education, cohabitation, marital status, working status and smoking, travel distance to hospital)	Patient questionnaire.	t1
	Clinical data related to diabetes and diabetes foot ulcer	Data from electronic medical journals at the clinical sites.	t1, t2,
	Consultations	Number in specialist care and primary care.	t2
	Wound classification [42,43]	University of Texas Diabetic Wound Classification System. Higher grade classified increasing wound depth (0-3). Higher stage classified the presence of infection and/or ischemia (A-D).	t1, t2

^a^t1: baseline assessment, t2: end of the initial follow-up period, t3: 36 months after end of the initial follow-up period, t4: will be merged with registry data after the trial is closed.

Long-term data on the time elapsing before a new foot ulcer appears and the incidence of amputation will be collected for 36 months after the initial follow-up period from the electronic patient journal at the clinical sites. Information on death (date and cause) will be retrieved from the Norwegian Cause of Death Registry.

#### Other Measures

We collect self-reported demographic data on age, sex, ethnicity, education, cohabitation, marital status, working status, and smoking status of the participant. In addition, clinical data are collected. For all participants, we store a picture and measure the wound area in the Web-based ulcer record system at the time of inclusion in the trial, after 8 weeks, and at the end of follow-up. The foot ulcers are classified according to the University of Texas Diabetic Wound Classification System [42], which combines grade and stage, is descriptive, and predicts clinical outcomes well (risk of amputation and healing time) [43]. At baseline, we collect data on blood pressure and measurements of neuropathy. Biological data include hemoglobin A_1c_ concentration and measurements of renal function (serum-creatinine, glomerular filtration rate, and microalbuminuria). Data from the medical records include type of diabetes, onset of diabetes, microvascular complications (retinopathy, neuropathy, and nephropathy) and macrovascular complications (myocardial infarction, stroke, claudication, and angina pectoris). Furthermore, we calculate the number of consultations, both in specialist health care and primary care.

### Sample Size

A statistical power analysis based on the primary outcome measure (healing time) was performed to decide the number of participants to be included using PASS sample size software, version 11 (NCSS, LLC). We powered the study to detect a difference in mean healing time larger than the selected noninferiority margin of 1.5 months [44,45], assuming 80% power, a significance level of .025, and a standard deviation of 3.6 months [46]. The analysis showed that on an individual level, a total sample size of 184 is needed. Considering an intraclass correlation coefficient of .02 and an average cluster size of 10 participants (design effect of 1.18), this number increased to 217 participants. As we expect an attrition rate of 5%, we aim to include 114 patients in each treatment group.

### Statistical Analysis

We will report descriptive statistics of baseline characteristics for the treatments groups including means and standard deviations (medians and interquartile ranges for continuous variables and numbers and percentages for categorical variables).

Noninferiority of the telemedicine intervention will be confirmed if the lower limit of the 95% confidence interval for the mean difference in healing time is less than 1.5 months. To account for correlated data introduced by the study design, we will apply the linear mixed-effects model [47] for this analysis. In addition, we will analyze group differences in time to healing with a proportional hazards model with adjustment of the standard error for clustered observations. Secondary outcome measures will be analyzed with superiority hypothesis tests. These tests will be based on either (generalized) mixed-effects models [47] or proportional hazards models (cluster) depending on the type of the outcome measure investigated. Estimated effect measures (absolute and relative) will be presented with 95% confidence intervals and *P* values.

Because our trial has a maximum follow-up period of 48 months, we expect some dropouts. We will perform intention-to-treat analyses and additional analyses based on the participants who actually participated actively in our trial during the 12-month follow-up period.

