### Aims and Research Questions

The main aim of this trial is to evaluate whether follow-up of patients with diabetes-related foot ulcers in primary care, in collaboration with hospital outpatient specialist care, is noninferior to standard outpatient care in terms of ulcer healing time.

Our primary research question is whether healing time (within 12 months) of diabetes-related foot ulcers treated in primary care in collaboration with telemedicine consultations with a hospital outpatient is no worse than with standard hospital outpatient care. The corresponding null hypothesis: mean difference in healing time is 1.5 months or less for diabetes-related foot ulcers with telemedicine follow-up in primary care, compared to standard hospital outpatient care.

We will also evaluate whether the incidence of amputation and mortality, sickness absence, clinical measures (number of consultations, complications directly related to the foot ulcer as indicated by use of antibiotics), recurrence of a new foot ulcer (within 48 months), and patient-reported outcome measures (PROMs) are different for telemedicine follow-up in primary care compared with standard hospital outpatient care.

We conducted supplementary qualitative studies to provide a more comprehensive description and evaluation of the ongoing processes during the intervention. Individual interviews with patients in the intervention and control groups aimed to explore patient experiences with telemedicine follow-up or standard outpatient care delivered in the DiaFOTo trial. Focus group interviews with health care professionals either working in primary care or in specialist care delivering the intervention aimed to explore health care professional experiences when they adopt this new technology in caring for patients with diabetes foot ulcers.

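### The noninferiority rule tests the lower confidence limit instead of the upper, so telemedicine passes unless it is proved worse than the margin

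*Protocol article*

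**What the plan says.** The primary outcome is "healing time measured from the time the person presents the ulcer at the clinical site" until the ulcer has healed (Primary Outcome Measure), so a larger value is worse. The research question is whether healing time under telemedicine "is no worse than with standard hospital outpatient care" (Aims and Research Questions).

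The only decision rule is in Statistical Analysis. Noninferiority is confirmed "if the lower limit of the 95% confidence interval for the mean difference in healing time is less than 1.5 months". That section does not say which arm is subtracted from which.

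Two other statements bear on the rule:

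- **Aims and Research Questions:** "The corresponding null hypothesis: mean difference in healing time is 1.5 months or less" for ulcers "with telemedicine follow-up in primary care, compared to standard hospital outpatient care".
- **Sample Size:** the trial is powered to detect "a difference in mean healing time larger than the selected noninferiority margin of 1.5 months", "assuming 80% power, a significance level of .025, and a standard deviation of 3.6 months". The section then states that "on an individual level, a total sample size of 184 is needed".

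**The concern.** To conclude that telemedicine is not worse by 1.5 months or more, the data must exclude every difference of 1.5 months or more. The whole confidence interval for telemedicine minus standard care must then lie below 1.5, and the limit that decides this is the upper one.

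The written rule looks at the other end. A lower limit below 1.5 means only that the data have not shown telemedicine to be worse than the margin. Absence of proof of harm beyond the margin would be reported as proof of noninferiority. An interval of 1.0 to 3.0 months, or of 1.4 to 3.5 months, would count as success.

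This sentence decides the trial's main conclusion. Followed literally, it has neither the error rate nor the power that the Sample Size section plans for.

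**Working it through.** **Inputs**

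- From Sample Size: margin 1.5 months, SD 3.6 months, significance level .025, power 80%, individual-level total 184 (92 per arm), intraclass correlation .02, average cluster size 10.
- Assumptions, not stated in the article: the .025 is one-sided, the true difference used for power is 0, and the difference is telemedicine minus standard care. The wording in Aims and Research Questions supports this direction but does not define it.

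**1. Reproducing the plan's sample size**

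The normal approximation for a noninferiority test gives, per arm,

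n = 2 × 3.6² × (1.96 + 0.842)² / 1.5² ≈ 90.4, rounded up to 91, or 182 in total.

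The t-based version gives 92 per arm, 184 in total, with 80.3% power. This matches the stated figure exactly. The alternatives do not: one-sided .05 gives 144 and two-sided .025 gives 220.

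The design effect is 1 + (10 − 1) × 0.02 = 1.18, and 184 × 1.18 = 217.1, which agrees with the stated 217.

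So the sample size belongs to a one-sided .025 noninferiority test at a true difference of 0.

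**2. Planned precision**

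SE = 3.6 × √(2/92) = 0.531 months. The 95% half-width is 1.96 × 0.531 = 1.04 months. Using 217 participants with the design effect gives the same SE.

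**3. What each rule accepts**

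- As written, lower limit below 1.5: estimate below 1.5 + 1.04 = 2.54 months.
- Upper limit below 1.5: estimate below 1.5 − 1.04 = 0.46 months.

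**4. Probability of declaring noninferiority at true difference D**

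As written: Φ((1.5 − D)/SE + 1.96). Upper-limit rule: Φ((1.5 − D)/SE − 1.96).

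| True difference (months) | As written | Upper-limit rule |
|---|---|---|
| 0 | >99.99% | about 80% |
| 1.5 (the margin) | 97.5% | 2.5% |
| 2.0 | 85% | 0.2% |
| 2.5 | 53% | about 0.01% |
| 3.0 | 19% | <0.01% |
| 3.5 | 3.5% | <0.01% |

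Taking the SE from the power statement instead, 1.5/(1.96 + 0.84) = 0.535, gives 54% at 2.5 months and 20% at 3.0 months. The other conclusions do not change.

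**5. Effect of lower precision**

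The acceptance threshold as written is 1.5 + 1.96 × SE, so it loosens as the trial becomes less precise. With half the information, SE = 0.531 × √2 = 0.751 and the threshold is 1.5 + 1.96 × 0.751 = 2.97 months. The chance of passing at a true difference of 2.5 months rises from 53% to Φ(−1/0.751 + 1.96) ≈ 73%. This matters because the Results section reports that early recruitment fell short.

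**6. The other direction of subtraction**

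With standard care minus telemedicine, the correct rule would be a lower limit above −1.5. If telemedicine is truly worse by D, the written rule passes with probability Φ((1.5 + 1.04 + D)/0.531). That is above 99.99% at D = 0 and essentially 100% at D = 1.5 or 3. The wording is wrong under either sign, and worse under this one.

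**The case against.** The strongest reply is that this is a slip of wording. The trial is described throughout as a noninferiority trial, and the sample size of 184 reproduces only under the correct test, so a competent analyst would probably use the upper limit. The point about intent stands, but a lone typing error cannot be assumed. The null hypothesis in Aims and Research Questions places differences of 1.5 months or less under the null, which is reversed for a noninferiority test. The Sample Size section describes power to detect a difference beyond the margin. The written rule amounts to failing to reject that reversed null, so three statements agree with one another and none gives the upper-limit rule.

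A second reply is that the rule is not without limit. With telemedicine minus standard care, it withholds noninferiority when the whole interval lies above 1.5, that is, when the estimate exceeds about 2.54 months. This is correct and bounds the concern. A noninferiority claim is almost certain for true differences up to the margin and becomes less likely beyond it.

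A third reply is that a separate analysis plan may hold the right rule. The article does not leave the rule open, however; it states it, and states it wrongly. A correct rule elsewhere would contradict this text, which would still need correcting.

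**Conclusion.** The concern holds. As written, the primary decision rule tests the wrong confidence limit. At the planned precision it declares noninferiority in 97.5% of trials where telemedicine is worse by exactly the margin, against a planned 2.5%. It does so in about 85% of trials at a true difference of 2.0 months and a little over half at 2.5 months. At no true difference the pass rate exceeds 99.99%, so the stated 80% power does not describe this rule either.

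These figures assume telemedicine minus standard care, a one-sided .025 level, a true difference of 0 for the power calculation, and a normally distributed estimate with the design SE. The level and the zero difference are inferred, but together they reproduce the stated 184. The finding that the rule is wrong does not depend on the assumed sign. It must be corrected before the analysis, because it determines the trial's main conclusion.

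**What to change.** Replace the decision rule in Statistical Analysis with:

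*Noninferiority will be concluded if the upper limit of the two-sided 95% confidence interval for the difference in mean healing time (telemedicine minus standard care) is below 1.5 months.*

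Align two other statements so that the corrected rule does not contradict them:

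- **Aims and Research Questions:** state the null as a difference (telemedicine minus standard care) of 1.5 months or more, and the alternative as a difference below 1.5 months.
- **Sample Size:** say that the trial has 80% power to show noninferiority at a margin of 1.5 months, with a one-sided significance level of .025. State the true difference assumed; 0 reproduces the figure given.

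If a separate analysis plan exists, check that it carries the same rule. The cost is a few sentences, dated before the analysis. The sample size, data collection and patients are unaffected: the corrected rule has the 2.5% error and roughly 80% power that the sample size was built for.

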### Qualitative Substudies

#### Patient Experiences

Some participants with diabetic foot ulcers receiving either the telemedicine follow-up in primary care in collaboration with outpatient specialist care or standard outpatient care were individually interviewed to explore their experiences with telemedicine follow-up or standard outpatient care delivered in the DiaFOTo trial. Interviewees were selected to ensure a diverse sample in terms of group (intervention vs control), age, gender, marital status, setting, and comorbid diseases. The study nurses at the clinical sites organized recruitment of the patients. Patients were included if their foot ulcers had healed or after the intervention was completed.

Data were collected using individual semistructured interviews. The interview guide contained eight overall topics with subthemes for the intervention group and seven overall topics with subthemes for the control group. The topics were similar for both groups, except the control group were not asked questions related to the telemedicine equipment and the health care professional’s attitudes on using images in wound care (Textbox 1).

Main topics in the interview guide (patient experience).Intervention groupPatient experience with the foot ulcer and what he/she did when he/she discovered the ulcerPatient experience of receiving telemedicine treatment and follow-up from the home care nursePatient experience of being followed up in specialist health carePatient experience of being involved in wound management and decisions that concerned his/her treatmentPatient experience with health care professional use of the telemedicine equipment and health care professional’s attitude on using images in wound carePatient-observed telemedicine collaboration between the home care nurse and specialist health care service during follow-upPatient perception of whether he/she takes more responsibility for his/her own healthPatient perception of the most important task home care nurses and experts at the outpatient clinic have in treatment and care of patients with diabetic foot ulcersControl groupPatient experience with the foot ulcer and what he/she did when he/she discovered the ulcerPatient experience of receiving traditional treatment and follow-up from the home care nursePatient experience of being followed up in specialist health carePatient experience of being involved in wound management and decisions that concerned his/her treatmentPatient-observed collaboration between the home care nurse or general practitioner and specialist health care services during follow-upPatient perception of whether he/she takes more responsibility for his/her own healthPatient perception of the most important task home care nurses and experts at the outpatient clinic have in treatment and care of patients with diabetic foot ulcers

Data were collected and interviews carried out until saturation was achieved, in line with recommendations existing for qualitative research [48]. Transcribed interview text was analyzed by developing codes, grouping similar codes together in larger groups, and exploring these for patterns in terms of similarities and differences. As relationships became apparent, we interpreted them from a clinical and theoretical perspective. Several researchers were involved to support reflexivity of researchers throughout all phases of the qualitative study. Researchers analyzed data separately first and then compared and contrasted their analyses to reach a consensus on main themes and subthemes. Interpretive description was used as a strategy in this study. This approach to qualitative knowledge development for applied clinical fields aims to produce new knowledge and a contextual understanding that can be put to direct applied use when implementing the intervention in future clinical practice [49,50].

#### Health Care Professional Experiences

Interpretive description was also used as a research strategy for this study. Health care professional experiences with the intervention were explored and Donabedian’s framework was used to structure essential components of health services to be addressed in the study [51,52]. Information on health care professional experiences was collected through focus group interviews among those working in primary care or in specialist care delivering the intervention. We mixed different health care professions within their own working context so that different perspectives within their context could be explored and discussed. The focus groups were conducted by a moderator and comoderator among health care professionals in the initial stages of introducing telemedicine in their work. The semistructured interview guide covered topics related to our study aim (Textbox 2).

Main topics in the interview guide (health care professional experience).Participant experience using telemedicine and how it was organized where they workParticipant experience using telemedicine as a new tool in documentation and communicationParticipant experience of communication and collaboration between outpatient clinic (physicians, nurses, and foot therapists) and nurses in home care through telecommunication and among professionsParticipant perception of changes in competence in caring for people with diabetes foot ulcers during the interventionParticipant perception of changes in job satisfaction while using telemedicine

